## Abstract

**Background:**

Despite its prevalent and impactful nature, dry mouth remains an underexposed and undertreated symptom in patients with a life-limiting condition or frailty. The main contributing factors are a lack of awareness and knowledge amongst both healthcare professionals and patients, and a scarcity of effective, evidence-based interventions. In the DRy mOuth Project (DROP), we address these factors by investigating both a non-pharmacological and a pharmacological intervention: a nurse-led patient education program and locally applied pilocarpine.

**Methods:**

This intervention-based research project consists of two parallel studies. The non-pharmacological study is a cluster non-randomized controlled trial in 228 palliative nursing home and hospital patients, investigating the effect of structured use of guidelines and of patient education on dry mouth symptoms. This intervention, a nurse-led patient education program (the Mouth Education Program, MEP), will be compared to care as usual, the control. The pharmacological study is a double-blind placebo-controlled randomized trial that examines the effect of locally applied pilocarpine drops in 120 patients with dry mouth symptoms. Both studies use the same mixed-methods study design, in which the primary outcome is the clinical response to the intervention at 4 weeks, as measured by a dry mouth severity score (numeric rating scale from 0 to 10). Other outcomes, as measured by questionnaires over a 12-week follow-up period, include durability of the effect, impact on quality of life and, adherence and acceptability of the intervention. In addition, the feasibility and cost-effectiveness are evaluated by means of questionnaires and focus groups with healthcare professionals, and interviews with patients.

**Discussion:**

This study investigates the effectiveness and feasibility of two interventions for dry mouth symptoms in patients with life-limiting conditions or frailty. Due to the large-scale and mixed-method nature of the study, this study will also improve our understanding of dry mouth and its relating factors and of the patients’ and healthcare professionals’ experiences with symptoms, care and guidelines of dry mouth, including any perceived barriers and facilitators.

**Trial registration:**

NCT05964959 & NCT05506137.

## Background

Xerostomia or dry mouth is a severely impactful yet underacknowledged symptom in patients with a life-limiting illness or frailty. It is often associated with alterations in the quality and quantity of saliva, which leads to functional alterations like halitosis, burning sensations, altered taste perception, pain, and difficulty in eating, swallowing and speaking [1, 2]. As such, xerostomia causes physical and emotional discomfort, thereby significantly reducing quality of life [2, 3].

Dry mouth complaints are very common in both older patients and patients in the last phase of their lives [4]. Xerostomia is present in 20 to 60% of the elderly [2, 5, 6], in 50 to 83% of cancer patients receiving palliative care [7–9] and in 60% to 85% of patients with advanced disease [1, 10]. Prevalence of xerostomia highly depends on patient characteristics: important causes are polypharmacy and anticholinergic drugs, aging salivary glands, various chronic diseases, chemotherapy, previous history of radiotherapy to the salivary glands in head and neck cancer and general poor health [2].

Despite its prevalent and impactful nature, dry mouth remains an undertreated symptom in patients due to two main barriers: limited attention to and recognition of dry mouth complaints amongst both health care professionals and patients themselves, and a lack of evidence-based, effective pharmacological interventions[4].

As for the first barrier, health care professionals are often aware of the importance of oral care and high prevalence of dry mouth symptoms in the palliative phase but experience difficulty in addressing and treating dry mouth in clinical practice [4, 11]. An important factor is a lack of training, resulting in limited knowledge and discomfort with performing oral care and oral health consultations [12–14]. Other contributing factors are a lack of uniform guidelines and protocols, and an unclear division of responsibilities [12, 13]. Furthermore, patients are often not aware of the options to ease their symptoms and do not know which healthcare professional they can turn to for their dry mouth problems [4, 14]. Current research, however, shows that participation in education programs about oral care by both patients and professional caregivers can be an effective intervention to improving oral health in general and dry mouth specifically. One meta-analysis showed that education programs for older patients with dry mouth increases oral salivary secretion and improves oral health related quality of life [15], while another meta-analysis showed that education programs for long-term nursing home caregivers increases normal, non-xerostomic oral mucosa and decreases detectable stomatitis in their patients [16].

The second barrier is the absence of effective, pharmacological treatments with limited to no side-effects. Aside from symptom management through lifestyle, dietary and oral hygiene improvement and/or short-lasting saliva substitutes, there is just one (off-label) pharmacological option available in the Netherlands and most other countries: pilocarpine [17–19]. Pilocarpine is a parasympathomimetic and systemic drug that activates muscarinic receptors, thus increasing the secretion of natural saliva and alleviating symptoms of dry mouth. Systemic pilocarpine, however, has been associated with severe side effects, such as excessive transpiration, headaches, dizziness and frequent urination. The severity of these side effects often do not outweigh the benefits of the drug [20]. Therefore, current research focuses on topical administration of pilocarpine in the oral cavity (e.g. lozenges, drops or mouthwash). This has indeed been identified as a potentially effective treatment option for dry mouth with significantly fewer to no adverse side effects [20–22]. In fact, a previous pilot study of our research group has found that locally administered pilocarpine drops are effective in reducing xerostomia complaints with minimal side effects in older patients with xerostomia [21]. While this and other recent studies show promising results for topical administration of pilocarpine in patients with dry mouth, there is currently insufficient high level evidence due to the use of small sample sizes and the lack of double-blind placebo randomized controlled trials.

The DRy mOuth Project (DROP) attempts to contribute to better care for patients with dry mouth in the last phase of life by addressing the above-mentioned barriers with two separate intervention studies. The first barrier, the lack of knowledge and awareness, will be addressed by investigating a nurse-led patient education program in a cluster mixed-methods trial. The second barrier, the lack of an effective pharmacological treatment, will be addressed by investigating a topical form pilocarpine in a double-blind placebo randomized controlled trial.

In this article, we describe the aim, design and procedures for the two studies of the DROP. In both studies, the interventions’ clinical effectiveness, practical feasibility and cost-effectiveness are assessed. The DROP aims to:investigate the effect of both a nurse-led patient education program and a local form of pilocarpine on dry mouth severity and oral health related quality of life;evaluate the feasibility and acceptability of both interventions; andexplore current experiences with dry mouth care and dry mouth care guidelines of both patients and health care professionals in palliative care.

## Methods

### Study design

The DROP consists of a non-pharmacological and a pharmacological intervention study.

Both studies are multi-center, prospective, intervention trials with a nested qualitative sub-study, investigating the effect of the interventions on dry mouth symptoms in patients with a life-limiting illness or frailty (see also Fig. 1).

**Fig. 1 Fig1:**
[figure not shown]
Study procedures for the non-pharmacological (**a**) and pharmacological study (**b**) within the Dry mOuth Project. **a** The Mouth Education Program (MEP) study is a cluster non-randomized trial with a study period of 12 weeks and five visits per patient. **b** The pilocarpine study is a double-blind placebo randomized controlled trial with an active treatment period of four weeks and an optional expanded access period of eight weeks per patient. **c** A nested qualitative sub-study will be conducted during and after both studies. Abbreviations: CAU = care as usual, MEP = Mouth Education Program, UC = usual care; HCP = health care professionals; T0-12 = patient timeline at *t* = 0, *t* = 2, *t* = 4, *t* = 8 and *t* = 12 weeks

#### Mouth Education Program (MEP) study

The non-pharmacological study is a cluster non-randomized trial with 228 patients divided over twelve clusters (twelve organisations) in two care settings: a hospital setting with six clusters and a nursing home setting with six clusters. Within each care setting, three clusters will be allocated to the intervention arm on a first come, first serve basis (114 patients), after which three clusters will be allocated to the control arm (114 patients). The intervention, the Mouth Education Program (MEP), will be compared to the control, care as usual (CAU) over a twelve-week period. A cluster non-randomized design was chosen to reduce between-condition contamination and to improve recruitment and logistic processes [23].

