#### MEP study

Within the MEP study, participating organizations are recruited through a regional network for nursing homes (University Network Care sector Zuid-Holland, UNC-ZH) and interprofessional connections with hospitals and nursing homes. Before the start of the study, all participating organizations are allocated to either the intervention arm (3 nursing homes, 3 hospitals) or control arm (3 nursing homes, 3 hospitals) on a first come, first serve basis (non-randomized).

Upon allocation to the intervention group, the participating nurses will first receive the MEP training before the inclusion of the first patient.

Eligible patients will be identified by the nurses and nurse specialists participating in the study with the help of the regular care teams on the wards of the hospitals and nursing homes. Identified patients will be provided with both oral and written information and an informed consent form on paper. After sufficient time for consideration (a minimum of 24 h), the patient will be asked to participate. Only after written informed consent, the study can commence.

Within the intervention group, all research questionnaires will be administered by the nurses as they are part of the anamnesis within the MEP consultation. Within the control group the questionnaires will be (telephonically) administered by a researcher.

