### Data analysis

#### Analysis of effect evaluation

All analyses will be carried out using statistical software that supports multi-level mixed model analyses, including the latest version of IMB SPSS Statistics. Demographic and baseline disease characteristic data will be summarized for each treatment group by presenting descriptive statistics. For continuous variables, we will use the mean and standard deviation (SD) in case of a normal distribution, or median and first and third quartile in case of skewed distribution. In case of missing data, we will use stochastic regression imputation to produce a synthetic part of the data to allow for an intention to treat analysis that includes all patients. For all analyses on primary and secondary outcomes a *p* value < 0.05 will be considered to indicate statistical significance. However, interpretation of these significant results will primarily focus on clinical relevance.

The primary outcome (percentage responders at 4 weeks) will be computed by using multi-level logistic regression analysis in the MEP study due to its cluster design, and linear regression analysis in the pilocarpine study taking the randomization stratification variable (sex) into account. Results will be expressed as odds ratio (OR) with a 95% confidence interval (CI).

All secondary outcome measures will be described in full using either mean and standard deviation median and interquartile range for continuous measures or count and proportion for categorical measures. Between-group differences in secondary outcomes at 4, 8, and 12 weeks (i.e., mean GOHAI-NL scores [33], mean PRFS scores [35], and patients’ Global Perceived Effect [37] dichotomized into success and no success) will be tested using multivariable generalized linear regression analysis with a link-function depending on the distribution of the variable (i.e. gaussian, or linear regression for continuous variables, binomial, or logistic regression for binary outcomes).

Cost-effectiveness analysis will be performed to examine both the costs and health outcomes of the interventions versus the control group, using the EQ-5D-5L [34], iMCQ [38] and factual costs of the medicine.

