### Limitations

This study does come with some methodological challenges. Recruitment difficulty and loss-to-follow-up due to frailty, deteriorating condition or death are specifically of concern with this palliative study population. By excluding terminally ill patients (life expectancy of 4 weeks or shorter), limiting the number of questionnaires (thus participation burden) and increasing the sample sizes, we hope to limit the impact of this concern.

However, recruitment is not only a concern within the patient population. The post-covid health care system is under great pressure in the Netherlands. Increased healthcare consumption paired with staffing problems due to high burn-out and other illness absence rates have led to increased work pressure and vice versa. This may impact health care professionals’ willingness to participate in the MEP study for which active participation and an additional time investment is needed. We attempt to address this pre-emptively by offering intensive and easily accessible support as well as a monetary stipend per included patient. As for the pilocarpine study, patients are provided with one-on-one instructions by the researchers to administer the drops themselves, to relieve their regular care team of potential extra tasks.

Regarding the cluster non-randomized design of the MEP study, a balance was sought between methodological strength and logistic constraint. A non-randomized design enables us to include care institutions more swiftly and easily (on a rolling basis) within a limited time frame, but may bring in some level of response bias. However, its cluster design limits the level of bias as it merely takes place on an organizational level, not on the patient or clinician level as with a patient-randomized trial.

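### MEP organisations are allocated by order of sign-up and patients are found by arm-aware nurses, but the stated primary MEP model deals only with clustering and the Limitations section understates the bias that remains

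*Protocol article*

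**What the plan says.** **Allocation.** The Study design section (MEP study) describes "a hospital setting with six clusters and a nursing home setting with six clusters". Within each setting, "three clusters will be allocated to the intervention arm on a first come, first serve basis (114 patients), after which three clusters" form the control arm. The Study procedures section (MEP study) repeats the rule: "control arm (3 nursing homes, 3 hospitals) on a first come, first serve basis (non-randomized". It places the allocation of all organisations before the study starts.

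**Recruitment.** The same section has MEP nurses trained before their first patient is included, and states: "Eligible patients will be identified by the nurses and nurse specialists participating in the study".

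**Analysis.** Under Analysis of effect evaluation, the MEP primary outcome "will be computed by using multi-level logistic regression analysis in the MEP study due to its cluster design". The same sentence gives "linear regression analysis in the pilocarpine study taking the randomization stratification variable (sex) into account". Secondary outcomes "will be tested using multivariable generalized linear regression analysis with a link-function depending on the distribution of the variable", without a list of covariates.

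**Available data.** NRS and patient-reported functional status are measured at week 0 (Table 2). Age, gender, care setting, primary diagnosis, co-morbidities and medication are listed under Baseline measures.

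**Stated limitation.** The Limitations section concedes some response bias from the non-randomised design, then argues that "its cluster design limits the level of bias as it merely takes place on an organizational level, not on the patient or clinician level", in contrast to a patient-randomised trial.

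**The concern.** Arm is fixed by when an organisation signs up. If sign-up time is related to how well an organisation's patients would respond anyway, that relation enters the MEP odds ratio. The protocol makes such a relation plausible. Its description of usual care says that institutions differ in awareness, knowledge, guideline use, training and resources, and its Limitations section says that work pressure may affect willingness to take part.

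A second route runs through patients. Recruiters know the arm, and only the MEP nurses have just been trained to recognise dry mouth, so the patients they find may differ in severity or diagnosis. The endpoint is a fall of at least 2 NRS points from a baseline of at least 5, so baseline NRS is an obvious prognostic variable.

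At stake is how the primary odds ratio is read. A larger sample narrows the interval around a confounded estimate without moving it.

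**Working it through.** **1. The plan's own figure.** 181 evaluable patients with 20% dropout: 181 / 0.80 = 226.25, so 227, rounded up to 12 × 19 = 228. This reproduces the stated total. It has no bearing on confounding.

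**2. What the model can do.** A random intercept assumes that the organisation effect is independent of arm. Allocation by sign-up order is what could break that assumption. Fixed organisation effects are no way out, because arm is constant within an organisation and would be aliased with them. Measured patient-level differences can be adjusted for; organisational motivation cannot, with six organisations per arm and no measure of it.

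**3. Illustration, organisation level.**
- From the Sample size section: ICC 0.10; planned difference 25 percentage points.
- Assumed: response rate 35% (no control rate is given); correlation r between sign-up order and an organisation's underlying response rate; no true MEP effect.
- Between-organisation SD = √(0.10 × 0.35 × 0.65) = 0.151.
- Expected mean of the top three minus the bottom three of six normal values = 1.406 SD.
- Bias = r × 1.406 × 0.151.

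| r (assumed) | Bias, percentage points | Share of 25 |
|---|---|---|
| 0 | 0 | 0% |
| 0.3 | 6.4 | 26% |
| 0.5 | 10.6 | 42% |
| 1 (extreme) | 21.2 | 85% |

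A negative r gives the same sizes with the opposite sign. The calculation also assigns the whole ICC to variation within a setting. If part of the 0.10 reflects hospital versus nursing home differences, these figures are too large, because allocation is within setting.

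**4. Effect on the test.** Mean evaluable cluster size is 181 / 12 = 15.08, so the design effect is 1 + 14.08 × 0.10 = 2.41 and the effective number per arm is 181 / (2 × 2.41) = 37.6. With no true effect and assumed control rates of 30 to 40%, a spurious 10-point difference raises the chance of a two-sided significant result from 5% to about 14 to 15%.

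**5. Illustration, patient level.** Assume a 1-point difference in mean baseline NRS between arms, a slope of 0.5 for NRS reduction on baseline, and an SD of 2.5 for the reduction. The mean reduction then shifts by 0.5 / 2.5 = 0.2 SD, and the responder rate moves by about 8 points from 35%. None of these inputs is in the protocol, and nothing there predicts an imbalance of that size. The example shows only why baseline NRS belongs in the model.

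**6. The limitation set against the procedures.** The Limitations section places bias at organisation level and treats that as reassuring. Organisation-level bias is the confounding in question, and a small number of organisations does not average out a systematic difference. The Study procedures section also has arm-aware nurses identifying patients, so bias at patient and clinician level is not excluded.

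**The case against.** The strongest reply is that the article names a class of model and does not forbid covariates. A covariate list is commonly left to an analysis plan, which is not shown. Sex is named for the pilocarpine study because it is the stratification variable there, and the secondary analyses are called multivariable. This stands in part: a reader might infer that the plan prescribes an unadjusted analysis, and the text does not say so. What remains is that clustering is the only reason given for the primary model of a non-randomised comparison. Moreover, the allocation rule and the reassurance in the Limitations section are fixed in this document whatever an analysis plan adds.

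Other stronger readings also go too far.
- *Care setting is confounded with arm.* It is split 3:3 in each setting with 19 patients expected per centre, so it is balanced by design if recruitment is even.
- *The keenest organisations receive MEP, so MEP is flattered.* Sign-up order may equally reflect contact order or local approval speed. Keen organisations may also give better usual care already, leaving less room to improve.
- *Cluster randomisation would cure everything.* Recruitment by arm-aware nurses would persist.

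The design is also openly declared non-randomised and given reasons, and usual-care data are collected to help explain results. Avoidance of contamination, however, justifies clusters and not the order in which they are assigned. The logistic reasons are real, but they do not support the claim that clustering limits the bias.

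**Conclusion.** The point holds in a bounded form. Allocation by sign-up order and recruitment by arm-aware nurses leave the MEP comparison open to confounding at organisation level and selection at patient level. The primary model as stated addresses neither, and the Limitations section's reassurance is unsound. That rests on the text alone.

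The size does not. The 6 to 11 points depend on an assumed 35% response rate, an assumed correlation of 0.3 to 0.5 and the whole ICC lying within setting. The bias could be zero or run against MEP. A reader should not infer that the MEP result will be overstated by a known amount, nor that covariate adjustment would make it equivalent to a randomised estimate.

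**What to change.** 1. **Primary MEP model.** Specify a multi-level logistic regression with fixed effects for arm, baseline NRS and a short prespecified list of visit-1 variables, for example age, sex, functional status and primary diagnosis in a few groups. Include care setting as a design and precision factor, not as a presumed confounder. Report the unadjusted odds ratio as secondary. Odds ratios change with adjustment even without confounding, so the gap between the two should not be read as the amount of bias.
2. **Limitations wording.** Replace the statement that clustering limits bias. Say that organisation-level confounding remains and cannot be removed by patient-level adjustment, that patient-level recruitment bias is possible, and that the MEP estimate is an adjusted non-randomised comparison.
3. **Allocation, only if still open.** For any organisation not yet allocated, draw the arm at random within setting; permuted blocks fit rolling entry. This is probably moot, since allocation is described as preceding the study and the Conclusion dates the start of recruitment to June 2023.

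Items 1 and 2 cost analysis-plan and article text and need no new data; they should be settled before outcome data are examined. Item 3 would cost some scheduling freedom.
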